#### Statistical analysis

Data will be analyzed using the statistical package SPSS 21.00 for Windows. Statistical significance will be set at *p* < 0.05. Prior to statistical comparisons, all data will be tested for normal distribution. Then, a descriptive analysis of the data will be obtained for the dependent variables in the different assessment times. Subsequently, homogeneity of the two intervention groups will be studied. To confirm if there are differences in each group (intra-group comparisons), considering each group in isolation, between the four assessments in each of the variables (baseline, post treatment, 3-month follow-up, 6-month follow-up), repeated measures analysis of variance ANOVA will be used. To calculate inter-group differences between baseline and follow-ups, a four-way repeated-measures ANOVA will be conducted, with the scores of every primary and secondary outcome as dependent factors, with four levels corresponding to every time of assessment (t1, t2, t3 and t4), and the two intervention groups (CNS-focused treatment vs standard care treatment) as independent factors. Between- and within-group effect sizes for all quantitative variables will be measured with the Cohen *d* coefficient. An effect size greater than 0.8 will be considered large, around 0.5 moderate, and less than 0.2 small [42]. In cases of missing data, an intention-to-treat analysis will be performed. Double data entry will be carried out in order to promote data quality.

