### Primary and secondary outcome measures and assessment points

The primary outcome measured is self-reported shoulder pain-related disability as measured on the Shoulder Pain And Disability Index (SPADI) questionnaire. The Spanish version of the SPADI has high internal consistency (Cronbach α: 0.916) and excellent test-retest reliability (ICC 0.91) [32]. Secondary outcomes are as follows:The Numeric Pain Rating Scale (NPRS), a valid and reliable measure of shoulder pain [33]Goniometric assessment of active shoulder ROM which is valid and reliable [34, 35]Two-point discrimination threshold measured at one standardize site on the affected shoulder (5 cm distal to the lateral border of the acromion) [36], following an established protocol [37]Laterality judgement accuracy using the NOI Recognize online program (www.noigroup.com) and following an established protocol [38]The Spanish version of the Tampa Scale of Kinesophobia, a valid and reliable measure of fear of movement [39]The Patient Specific Functional Scale, a reliable, valid and responsive instrument that can be used in patients with a primary shoulder complaint [40]

Assessment will occur at baseline, at the end of the treatment program (week 10), and at 3 and 6 months’ follow-up. At baseline, a clinical assessment of symptom distribution, history of the present and previous shoulder complaints, red flag screening, medical history and general health status will also be performed.

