### Statistical analysis including sample size calculation

#### Sample size calculations

The sample size will be calculated using G*Power 3.0.18 Software based on the SPADI as the primary outcome measure. To our knowledge, there are no studies investigating the effects of GMI or graded sensory discrimination training on FS. Based on similar studies applying physiotherapy on FS (SPADI mean of 66 points; standard deviation (SD) = 16) [8], and the minimal detectable change attained in the study by Tveita et al. (17 points) [41], to detect a 17-point (SD = 16) between-group difference, with 80% power and an alpha level of 0.05, a total sample size of 30 patients is estimated (15 per group). An allowance will be made for a 15% dropout rate, increasing the sample size to 34 patients (17 per group). However, since this calculation is not based in the use of GMI, to assure an adequate sample size, we will carry out a pilot study with 20 participants (10 per group) to test these assumptions. Mean differences and standard deviations from the inter-group comparison on the primary outcome (SPADI) will then be used to recalculate the sample size, if necessary.

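### SPADI has no primary visit or deciding ANOVA term, although the sample size assumes a single two-group comparison at alpha 0.05

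*Protocol article*

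**What the plan says.** All of the text is in the protocol article.

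- **Primary outcome** (section Primary and secondary outcome measures and assessment points). The definition given there reads: "The primary outcome measured is self-reported shoulder pain-related disability as measured on the Shoulder Pain And Disability Index (SPADI) questionnaire". No time point is attached.
- **Visits** (same section): "Assessment will occur at baseline, at the end of the treatment program (week 10), and at 3 and 6 months’ follow-up". The three post-baseline visits have equal standing.
- **Sample size** (Sample size calculations): the trial is sized "to detect a 17-point (SD = 16) between-group difference, with 80% power and an alpha level of 0.05", and the result reported from this is "a total sample size of 30 patients is estimated (15 per group"). The visit at which the difference should exist is not stated. A 20-participant pilot will then supply between-group SPADI differences and standard deviations for a recalculation, again with no visit named.
- **Analysis** (Statistical analysis): a general threshold of p < 0.05, then "To calculate inter-group differences between baseline and follow-ups, a four-way repeated-measures ANOVA will be conducted", with four time levels and two groups, for every primary and secondary outcome. The model is called four-way although it has one group factor and one time factor, so the label does not show which term decides.

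**The concern.** The article fixes a primary outcome, a sample size and a between-group analysis, and the three do not fit together. The sample size is for one comparison. The analysis is aimed at follow-up differences in the plural, and nothing says which result answers the question of effectiveness.

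The Significance and implications section expects the trial to show whether the CNS-directed program is more effective and also to inform on persistence to 6 months. If the groups differ at one visit and not at the others, the plan as written cannot say whether the trial succeeded. A claim could then rest on a visit or model term picked after the results were seen, and the nominal 0.05 would not be the chance of a false claim on the primary outcome.

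The gap also reaches the size of the trial. The pilot-based recalculation needs one mean difference and one standard deviation, and without a named visit that input is undefined.

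**Working it through.** **Inputs.** From Sample size calculations: difference 17, SD 16, power 80%, alpha 0.05, 15 evaluable per group, 17 per group enrolled. From the outcomes section: three post-baseline visits. From Statistical analysis: four time levels, two groups, p < 0.05. The article does not give the between-visit correlation of SPADI, so it is an assumption, varied from 0 to 0.9.

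**1. The plan's own figure.** d = 17/16 = 1.0625. A two-sided two-sample t-test at 0.05 with 80% power needs n = 14.93, so 15 per group (power 80.2%). This matches the stated 30. A one-sided test would need 12 per group and does not match. The figure is therefore one two-sided comparison, with no allowance for several visits and no use of repeated measures.

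**2. If the interaction alone decides.** Simulated null trials, 15 per group, four equally correlated visits, F test on 3 and 84 degrees of freedom: about 5% false positives. If visit contrasts are read only after a significant interaction, the chance of a claim is about 4%.

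**3. If the group effect or the interaction may count.** For two independent tests, 1 − 0.95² = 9.75%. Simulation gives 9% to 10%.

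**4. If a win at any of three visits may count, raw scores.** If the visits were independent, 1 − 0.95³ = 14.3%. With a common correlation ρ, let φ and Φ be the standard normal density and distribution function. The risk is

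1 − ∫ φ(u) [Φ((1.96 − √ρ·u)/√(1−ρ)) − Φ((−1.96 − √ρ·u)/√(1−ρ))]³ du

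| ρ | Risk of at least one false positive |
|---|---|
| 0 | 14.3% |
| 0.3 | 13.6% |
| 0.5 | 12.5% |
| 0.7 | 10.9% |
| 0.8 | 9.8% |
| 0.9 | 8.4% |

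Simulated t-tests at 15 per group agree closely (for example 13.6% at 0.3 and 8.4% at 0.9). The risk passes 10% only when ρ is below about 0.79.

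**5. The same rule on change from baseline.** With equally correlated visits, two changes sharing a baseline have covariance σ²(1 − ρ) and variance 2σ²(1 − ρ). They correlate at 0.5 whatever ρ is, so the risk hardly depends on ρ. Simulation gives 12.6% to 13.0%.

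**6. Sample size under each remedy.** One named contrast: alpha stays at 0.05, and 15 per group gives the 80.2% of step 1. If a win at any visit were kept with a Bonferroni correction, each test would use 0.05/3 = 0.0167. Power per visit would then be 64% with 15 per group and 71% with 17. Reaching 80% would need 21 per group: 42 evaluable, and 42/0.85 = 49.4, so 50 enrolled.

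**The case against.** A reader might infer that SPADI will be tested separately at three visits, each at 0.05, and that the false-positive risk is therefore more than doubled. The article does not support this. It plans one repeated-measures ANOVA per outcome, and its wording on differences between baseline and follow-ups fits a single group-by-time test. It announces no visit-wise test and no rule that any one visit counts as success. If the interaction decides, the risk is about 5%. Doubling needs ungated visit tests and, on raw scores, a correlation below about 0.79, which the article does not give. This part of the objection stands, so the size must be stated conditionally.

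It can also be said that this is a condensed article and that post-hoc contrasts, multiplicity adjustment and the deciding model term are often left to a statistical analysis plan. That is fair for those details taken singly. It does not cover the primary time point, which belongs in the protocol, and the article itself states a sample size for one comparison beside an analysis of several follow-ups.

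Finally, week 10 is not the only sensible choice. The article stresses persistence to 6 months, and its training stages may be extended when accuracy is below 80%, so some participants may not have finished every stage by week 10. This also stands: the documents do not dictate the visit. They leave it open, and that is the defect.

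**Conclusion.** The point holds in conditional form. No primary visit or deciding ANOVA term is fixed for SPADI, while the sample size is for a single two-sided comparison. As written, more than one result could carry the effectiveness claim.

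The false-positive risk on SPADI is:

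- about 5% if the interaction alone decides;
- about 9% to 10% if the group effect or the interaction may count;
- about 8% to 14% on raw scores, or about 13% on change from baseline, if a win at any visit may count.

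These figures assume normal data, 15 per group and equally correlated visits. The raw-score range also rests on an assumed correlation. This should be corrected before the data are examined. It does not show that the planned ANOVA is invalid or that the error rate is inflated under every reading.

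**What to change.** Name one primary contrast in the protocol and the registry. One suitable choice is the between-group difference in SPADI at week 10, adjusted for baseline SPADI and tested once at two-sided 0.05. Week 10 is the scheduled end of the program and of the period in which participants are asked to avoid other shoulder treatment. The sponsor may choose another visit, provided it is fixed in advance.

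Use that contrast for the pilot-based recalculation, so that its mean difference and SD are defined. Treat SPADI at the remaining visits as secondary. Testing those visits only after a significant primary result, and reporting the other outcomes without confirmatory claims, are optional additions.

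The cost is a short amendment to the outcome, sample size and analysis text. N is unchanged (30 evaluable, 34 as planned). The small downside is that an effect seen only at another visit becomes a secondary result.

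### Intention-to-treat is offered as a response to missing data, and the named repeated-measures ANOVA falls back to complete cases unless an unstated imputation step is added

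*Protocol article*

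**What the plan says.** Four statements in the protocol article bear on this point.

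- **Missing data.** The Statistical analysis section has one sentence on the subject: "In cases of missing data, an intention-to-treat analysis will be performed". Nowhere else does the article mention intention-to-treat, and nowhere does it name imputation, carry-forward or a model that tolerates missing visits.
- **Between-group analysis.** The same section says: "To calculate inter-group differences between baseline and follow-ups, a four-way repeated-measures ANOVA will be conducted". Time enters "with four levels corresponding to every time of assessment (t1, t2, t3 and t4", and the two intervention groups are the between-subject factor. The software is fixed too: "Data will be analyzed using the statistical package SPSS 21.00 for Windows". A separate sentence, "repeated measures analysis of variance ANOVA will be used", covers the within-group comparisons only.
- **Visits.** The section on outcome measures and assessment points says: "Assessment will occur at baseline, at the end of the treatment program (week 10), and at 3 and 6 months’ follow-up". There are therefore three visits after baseline.
- **Expected loss.** The Sample size calculations section says: "An allowance will be made for a 15% dropout rate". Incomplete participants are therefore foreseen.

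**The concern.** Intention-to-treat is a rule about the analysis population: everyone randomised is analysed in the group to which they were allocated. It holds with complete data as much as with incomplete data. It does not say what to do about an outcome that was never observed. The article makes it conditional on data being missing and presents it as the remedy.

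The named analysis then pulls the other way. The standard repeated-measures ANOVA in SPSS works on one complete row per participant and removes anyone with a gap at any of the four assessments. This is a property of the method; the article does not state it. A participant who attended at week 10 and missed 6 months would then be lost from the week-10 comparison as well, although that value was recorded.

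What is at stake is the primary comparison on SPADI. If people who leave do worse or better than those who stay, and more so in one arm, excluding them biases the estimated difference. Enlarging the sample for dropout does not remove that bias. The sentence also leaves the treatment of incomplete participants to be chosen after the data are in.

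**Working it through.** **Inputs.** From Sample size calculations: difference 17 points, SD 16, 80% power, alpha 0.05 ("to detect a 17-point (SD = 16) between-group difference, with 80% power and an alpha level of 0.05"); 30 evaluable (15 per group), raised to 34 (17 per group) for 15% dropout. From the assessment schedule: three post-baseline visits. Missingness per visit is not given, so 5%, 10% and 15% are assumptions.

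**Step 1: reproduce the plan's figure.** Standardised difference d = 17/16 = 1.0625. Power comes from the noncentral t distribution, two-sided, with noncentrality d × √(n1·n2/(n1+n2)) and n1+n2−2 degrees of freedom. For 15 per group the noncentrality is 1.0625 × √7.5 = 2.91 and power is 0.802. The planned 15 per group is reproduced. The article does not say whether the test is one- or two-sided. A one-sided test would need 12 per group, so the two-sided version is the one used. For dropout, 30 × 1.15 = 34.5, taken as 34.

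**Step 2: power by number analysed.** These figures are for the design's own two-group comparison, not for the ANOVA's group-by-time term.

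| Situation | Analysed | Power |
|---|---|---|
| All randomised, all with outcomes | 34 (17/17) | 0.852 |
| Planned 15% total loss: 34 × 0.85 = 28.9 | 29 (14/15) | 0.787 |
| 5% missing independently per visit: 34 × 0.95³ = 29.2 | 29 (14/15) | 0.787 |
| 10% missing independently per visit: 34 × 0.90³ = 24.8 | 25 (12/13) | 0.720 |
| 15% missing independently per visit: 34 × 0.85³ = 20.9 | 21 (10/11) | 0.636 |

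**Step 3: how far this depends on independence.** Independent misses spread the gaps over the most people. If the same 10% miss every follow-up, complete cases are 34 × 0.90 = 30.6, about 31, which is not below the 30 that the design asks for. At 10% per visit, the number of complete cases therefore runs from about 25 to about 31, according to how far the misses fall on the same people.

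**Step 4: an illustration of bias.** Suppose 3 of 17 in one arm are lost and their true SPADI would have been 16 points (1 SD) worse than that of the completers. The completers' mean then differs from the full-arm mean by 3/17 × 16 = 2.8 points in that arm's favour, and 2.8/17 is about one sixth of the target difference. The between-group difference carries all of this only if the other arm has no such loss. With equal loss of the same kind in both arms it cancels.

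**Step 5: the two instructions side by side.** One sentence promises intention-to-treat when data are missing. The other names a method that needs all four values. Filling in the missing values first would satisfy both, but no such step is stated. Without it, the only analysis that the text defines runs on complete cases.

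**The case against.** The strongest reply is that a reader who infers a flat contradiction, or a declared complete-case plan, goes too far. That reply is right. Imputing missing visits and then running the ANOVA would honour both sentences, and the authors may have used intention-to-treat as shorthand for such a step. The article nowhere speaks of complete cases, listwise deletion or a per-protocol set, and its one sentence on missing data points towards keeping participants. Complete-case analysis is the default of the named method, not a stated intention.

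A second reply is that the choice of imputation or model is commonly left to an analysis plan or full protocol, neither of which is shown. Ethics and dissemination does refer to a full protocol and statistical code. This would answer a complaint about missing detail. It does not answer the point here, because the sentence that is printed misdescribes intention-to-treat, and the method that is printed handles incomplete participants poorly.

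A third reply concerns size, and most of it stands. The planned loss is already in the 34, so power at 15% total loss is barely below target. The lower figures need independent misses, and Recruitment procedures plans repeated email reminders and telephone calls. Treatment burden alone does not imply unequal dropout, because the standard-care arm has sessions of the same number and duration and a comparable home load. What remains is that the arms receive different care and that participants are asked to avoid other shoulder treatment for 10 weeks. Loss related to response, or unequal between arms, is therefore possible but not shown.

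**Conclusion.** The point holds in a limited form. The sentence on intention-to-treat is wrong as written, and the named between-group ANOVA falls back to complete cases unless a step that the article does not state is added.

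The main risk is bias, and the documents do not allow it to be sized. The 2.8 points is an illustration that rests on one-sided loss of participants who do 1 SD worse.

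A reader might infer that the trial is underpowered because of this. The figures do not support that: power is about 0.79 at the planned 15% loss, against the 0.80 target. The 0.85 for all 34 is a ceiling, since no method recovers outcomes that were never recorded. The fall to 0.72 rests on the assumption of 10% missing independently at each of three follow-ups.

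**What to change.** Three changes to the Statistical analysis section:

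1. State that all randomised participants are analysed in their allocated group, whether or not data are missing.
2. Replace the between-group repeated-measures ANOVA with a likelihood-based mixed model for repeated measures that uses every available visit. It is valid if data are missing at random, and SPSS offers it. Keeping the ANOVA is acceptable if multiple imputation is named as the step before it.
3. Add one sensitivity analysis for data missing not at random, with the shifts in SPADI fixed in advance. The article gives no basis for particular shift values, so the trial team must choose and justify them.

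The cost is wording and a little more analysis work. No new data are needed. The missing-at-random assumption cannot be tested from the data, which is why the third item is needed.

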### Data management

Data from the study will be only accessible to the research team and will be stored on password-protected computers at the University of Valencia. Paper-form data will be stored in locked cabinets located at the Department of Physiotherapy of that same university. In order to preserve data confidentiality study participants will be assigned an identification number which will be kept for the duration of the study. A list of participant identification numbers will be created and separated from the de-identified data. Statistical analyses will be performed keeping participant anonymity by using patient identification numbers and the statistician will be blinded to group allocation. Confidentiality will also be preserved when disseminating results by using group data.

### Significance and implications for practice

Preliminary data suggest that treatments that target CNS function are a promising approach to the treatment of people with shoulder pain including patients with FS. In the context of modest effects from most available physical therapy treatments for FS, this CNS-focused approach may lead to improved clinical outcomes. The trial should determine if the CNS-directed program is more effective than traditional interventions at reducing pain intensity and improving function in a FS cohort and will follow up participants for 6 months, providing important information on the persistence of any treatment effects. The inclusion of variables related to functional reorganization of the brain, such as the two-point discrimination threshold and laterality judgement accuracy, will also allow for the first time to explore responsiveness to change of these tests after treatment in a population with shoulder pain. In addition, this study provide a good oportunity to explore the relationship between shoulder pain, cortical changes and clinical markers in people with FS. Finally, the flexible structure of the interventions comprising the CNS-focused approach closely reflects the real-world clinical practice.

CNS-directed interventions constitute a completely new treatment paradigm for the management of shoulder pain and, in particular, people with FS. Feelings of stiffness in the back have been recently demonstrated to be a multisensory perceptual inference consistent with protection rather than reflecting biomechanical properties of the back [43]. Stiffness is a main characteristic in people with FS and the prevailing view is that it is related to a capsular fibrosis despite the cause being still unknown [44]. The positive effects in ROM observed in preliminary research conducted in people with FS after brief interventions targeting the CNS challenge the prevailing view that stiffness in FS is an isomorphic marker of the biomechanical characteristics of the shoulder. The results of this study should have the potential to address this issue and change the current physiotherapy management of FS.

